## Abstract

**Background:**

Sleep disturbances post concussion have been associated with more frequent and severe concussion symptoms and may contribute to poorer recovery. Cognitive behavioral therapy for insomnia (CBT-I) is an effective treatment for insomnia; however, it remains unclear if this treatment method is effective in improving sleep outcomes and reducing concomitant postconcussion symptoms.

**Objective:**

The hypotheses for this study are that (1) CBT-I will improve sleep outcomes and (2) CBT-I will improve concomitant postconcussion symptoms.

**Methods:**

In total, 40 individuals who are within ≥4 weeks of postconcussion injury and have insomnia symptoms will be enrolled in this randomized controlled trial. Participants will be randomized into either a group that starts a 6-week CBT-I program immediately after baseline or a waitlist control group that starts CBT-I following a 6-week waiting period. All participants will be reassessed 6, 12, and 18 weeks after baseline. Standardized assessments measuring sleep outcomes, postconcussion symptoms, and mood will be used. Linear regression and *t* tests will be used for statistical analyses.

**Results:**

Enrollment of 40 participants was completed July 2022, data collection will be completed in November 2022, and publication of main findings is anticipated in May 2023. It is anticipated that participants experience reduced insomnia symptoms and postconcussion symptoms following CBT-I and these improvements will be retained for at least 12 weeks. Additionally, we expect to observe a positive correlation between sleep and postconcussion symptom improvement.

**Conclusions:**

Successful completion of this pilot study will allow for a better understanding of the treatment of insomnia and postconcussion symptoms in individuals following a concussion.

**Trial Registration:**

ClinicalTrials.gov NCT04885205; https://clinicaltrials.gov/ct2/show/NCT04885205

**International Registered Report Identifier (IRRID):**

DERR1-10.2196/38608

## Introduction

### Background

Between 1.7 and 3.8 million people in the United States experience a concussion each year, and the prevalence of concussions continues to increase [1-3]. A concussion injury results from a rotational or linear force to the head, neck, or face, causing injury to the brain [2,4]. Injuries from a concussion result in a number of symptoms termed *postconcussion symptoms* [5], which can be categorized into 4 different domains: somatic, cognitive functioning, mood regularity, and sleep dysregulation [5].

Sleep dysregulation is a risk factor for prolonged recovery. One recent systematic review found that poor sleep was predictive of poor long-term outcomes in the acute phase of concussion recovery [6], while another systematic review found that poor sleep in the chronic phase of recovery was associated with poor cognitive functioning (executive function and working memory) and emotional regulation [7]. Currently, it is unknown if treatment for sleep disturbances in individuals with a concussion could impact recovery.

The causes of sleep disturbances are multifactorial. Axonal damage that occurs during the concussion injury can result in dysregulation of the sleep and arousal centers in the brain [6,8-11]. Furthermore, medication use, new onset or increase in anxiety or depression, or a change in routine and the sleep schedule can contribute to sleep disturbances [6,12,13]. Sleep complaints can be present immediately following a concussion or within the first few days or weeks following the injury. The most reported sleep disturbance in individuals with a concussion, insomnia, is experienced by nearly 50% of those individuals [14]. Chronic insomnia is defined as difficulty in falling asleep or staying asleep 3 or more days a week for more than 3 months [15,16].

Chronic insomnia following a concussion can result in elevated plasma levels of neurofilament light (NfL) and tau biomarkers [17]. Both NfL and tau biomarkers have been associated with axonal damage, neuronal injury, and neurodegeneration [18]. Additionally, these biomarkers have been associated with cognitive decline and cognitive impairment [18]. Emerging research has found higher levels of plasma NfL and tau biomarkers in individuals with a history of a concussion, who also have poor sleep [19]. A possible mechanism for why these biomarkers are elevated could be disruption in the regular sleep function of metabolic waste clearance through the glymphatic system [19]. It is hypothesized that by improving sleep, metabolic waste clearance within the glymphatic system will be enhanced, which could decrease the accumulation of the NfL and tau biomarkers.

To assist in improving insomnia symptoms, cognitive behavioral therapy for insomnia (CBT-I) is the recommended first-line treatment. CBT-I consists of a multicomponent program that includes cognitive and behavioral strategies targeted to address the perpetuating factors of insomnia [20]. CBT-I is more effective than pharmaceuticals for long-term treatment of insomnia [21,22]. Systematic reviews [23,24] and meta-analyses [25,26] have found that CBT-I has a medium to large effect size in various comorbid populations and diagnoses. A recent scoping review reported that cognitive behavioral therapy (CBT) improved sleep efficiency and sleep quality and reduced insomnia symptoms in individuals with traumatic brain injury of all severities [27]. Furthermore, there was a reduction in concomitant symptoms, specifically anxiety and depression, after completion of the sleep intervention [27].

To date, only one study has evaluated the use of CBT-I in individuals who sustained a concussion [28]. The main findings from this study (n=24) indicated that CBT- I improved insomnia symptoms and sleep quality and decreased dysfunctional beliefs about sleep in adolescents but did not improve anxiety, depression, and postconcussion symptoms following CBT-I. However, a small sample size limits the interpretation of these results. Therefore, an adequately powered clinical trial is needed to evaluate if CBT-I enhances sleep outcomes in people with a concussion and impacts the recovery process.

### Objectives and Hypotheses

#### Aim 1: To Assess the Therapeutic Effect of CBT-I in Individuals With a Subacute Concussion and Symptoms of Insomnia on Sleep Outcomes

We hypothesize that CBT-I will result in a greater magnitude of change in insomnia severity and sleep quality compared to the waitlist control (WLC). Furthermore, we hypothesize that the magnitude of change in insomnia severity and sleep quality will be maintained for 12 weeks following CBT-I.

#### Aim 2: To Assess the Therapeutic Effect of CBT-I in Individuals With a Subacute Concussion and Symptoms of Insomnia on the Severity and Number of Postconcussion Symptoms, Anxiety, and Depression

We hypothesize that CBT-I will result in a greater magnitude of change in the severity and number of postconcussion symptoms, anxiety, and depression compared to the WLC.

#### Aim 3: To Evaluate the Relationship Between Improvement in Sleep Outcomes and Postconcussion Symptoms

We hypothesize that improvement in insomnia severity will be positively associated with reductions in the severity and number of postconcussion symptoms.

#### Exploratory Aim: To Evaluate the Therapeutic Effect of CBT-I in Individuals With a Subacute Concussion and Symptoms of Insomnia on Levels of NfL and p-tau Biomarkers.

We hypothesize that there will be a significant reduction in plasma NfL and p-tau levels from baseline to post CBT-I.

## Methods

### Study Overview

The proposed study is a delayed-start randomized controlled trial of 6 weeks of CBT-I among individuals with a concussion, aged 18-64 years old (n=40; Figure 1). Individuals who meet the inclusion criteria (Textbox 1) will be randomized into 2 groups. The first is a CBT-I initial group (CBT-I initial; n=20), which will start the CBT-I intervention directly after completing the baseline assessment. The second group is the WLC group (n=20), which will start the CBT-I intervention 6 weeks after the baseline assessment. The final 6 weeks for all participants, regardless of group assignment, will include participation in typical activities such as maintaining employment status, family roles, etc. 

**Figure 1 figure1:**
[figure not shown]
Study flowchart. CBT-I: cognitive behavioral therapy for insomnia.

Inclusion and exclusion criteria.
**Inclusion criteria:**
Aged 18 to 64 yearsWithin ≥4 weeks of concussion injurySelf-report difficulty falling asleep, maintaining sleep, or waking up too early at least 3 nights per week since injuryScore of ≥10 on the Insomnia Severity Index to indicate clinical insomnia [29]Score of ≥17 on the Mini-Mental State Examination-Telephone questionnaire [30]
**Exclusion criteria:**
Known untreated sleep disorder (such as sleep apnea, restless leg syndrome, circadian rhythm disorder, hypersomnia, or parasomnias)Increased risk obstructive sleep apnea (score≥3 on the snoring, tiredness, observed apnea, high BP, BMI, age, neck circumference, and male gender questionnaire) [31,32]Increased risk of restless leg syndrome on the Restless Leg Syndrome Diagnosis Index [33]Increased risk of circadian rhythm sleep-wake disorder [34]Increased risk of parasomnia [34]Active abuse or history (up to 2 years) of alcohol or drug dependence as defined by the Diagnostic and Statistical Manual of Mental Disorders, Fifth Edition criteria [35]Severe mental illness such as schizophrenia or bipolar disorderScore of >29 on the Beck Depression Inventory or indication of suicidality (response of “2” or “3” to item 9) [36]History of diagnosed nervous system disorders other than concussion (such as multiple sclerosis, Parkinson disease, or stroke)Currently works in a night shift

### Ethical Considerations

This study was approved by the institutional review board at the University of Kansas Medical Center (STUDY00146439) and was conducted in accordance with the ethical standards of the Helsinki Declaration.

### Recruitment

Recruitment will primarily be carried out through physician referral at the concussion management clinic at the University of Kansas Medical Center (KUMC). Potential participants will also be contacted through the KUMC Heron Data Repository/Pioneers participant registry [37]—a registry of patients from the University of Kansas Health System who have given consent to be contacted for potential research. If the number of participants cannot be reached through these primary methods, participants will be sought from other concussion clinics in the Kansas City area, in community support groups, and through social media.

### Screening Procedures

Individuals will undergo a 2-step screening process. The first portion will consist of a standard telephone screening, which includes a review of the inclusion and exclusion criteria (Textbox 1); Insomnia Severity Index (ISI) [29] to assess insomnia symptom severity; snoring, tiredness, observed apnea, high BP, BMI, age, neck circumference, and male gender questionnaire to assess risk of sleep apnea [31,32]; the Restless Leg Syndrome-Diagnostic Index to assess for risk of restless leg syndrome [33]; and the Clinical Interview for Sleep Disorders-Revised [34] questionnaire to assess for circadian rhythm disorders, nightmare disorder, night terror disorder, and REM sleep behavior disorders. The Mini-Mental State Examination Telephone [30,38] will be administered for a cognition screen for informed consent purposes. The second step to the screening process will be to administer the Beck Depression Inventory (BDI) [36] by emailing the potential participant a link to complete the BDI using the Research Electronic Data Capture (REDCap) database [39,40]. The principal investigator, RL, will review the completed BDI to ensure eligibility. If participants are eligible, a link to complete the consent process via REDCap will be emailed to each prospective participant. After the consent process is completed, the participant will be emailed a link to complete the baseline assessments.

### Assessments

#### Overview

The baseline assessments will be sent via a REDCap survey within 2 days of the main consent completion. The baseline evaluation will consist of demographic information collection and a completion of questionnaires to assess sleep outcomes, postconcussion symptoms, and mood.

#### Demographics

The following demographic data will be collected via self-report during baseline assessment: sex, education level, ethnicity, race, marital status, number of physician-diagnosed concussions, mechanism of concussion injury, list of current medications and dosage of those medications, list of health care services currently receiving, and a question asking if insomnia started before or after the concussion injury.

#### Sleep Questionnaires

The ISI [29] is a valid and reliable measure of insomnia severity that consists of 7 questions, each rated on a scale of 0-4. The range of scores on the ISI is 0-28; a score of ≥10 suggests clinical insomnia [41]. The ISI completed at screening will be considered the baseline ISI score.

The Pittsburgh Sleep Quality Index (PSQI) will be used to assess quality of sleep [42]. Scores range from 0-21, with a higher score indicating lower quality of sleep. A global score of > 5 indicates poor sleep quality.

#### Postconcussion Symptom Severity Questionnaires

Postconcussion symptom severity and the number of symptoms will be assessed using the Post-Concussion Symptom Scale (PCSS) [43]. The severity of 22 concussion-related symptoms is assessed on a Likert scale ranging 0-6 with 0=“no symptom” and 6=“extreme symptom” [44]. A score of 132 is the maximum, indicating that all symptoms are severe [44]. The number of postconcussion symptoms will be assessed by counting the number of symptoms that the participant identified as having a severity of 1 or higher on the PCSS. A score of a 1 indicates that the symptom is mild but still noticeable.

#### Mood Questionnaires

The BDI [36] assessment will be used to assess the level of depression. The tool consists of 21 items that are scored on a Likert scale of 0-3 with 0=“no change in symptom” and 3=“severe change in symptom.” Scores range from minimal depression (0-13), mild depression (14-19), moderate depression (20-28), and severe depression (>29).

The BDI completed during screening will yield the baseline BDI score. The Beck Anxiety Inventory (BAI) [45] assessment will be used to assess the level of anxiety. The tool consists of 21 items that are scored on a Likert scale of 1-3 with 0=“not at all” and 3=“severely.” Scores range from minimal anxiety (0-7), mild anxiety (8-15), moderate anxiety (16-25), and severe anxiety (>30).

#### Blood Plasma Biomarkers

Blood plasma biomarkers will be assessed at baseline for all individuals enrolled and within 1 week of completing the CBT-I intervention. A trained phlebotomist will draw blood (~10 mL) into a vacutainer tube containing EDTA as an anticoagulant. The EDTA tube will then be inverted several times to mix prior to centrifugation at 1500 *g* for 10 minutes at 4 °C. After processing, plasma will be transferred into aliquots and stored at –80 °C until analysis. NfL and p-tau analysis will use Single Molecule Array analytics (Quanterix).

#### Reassessments

Reassessments will occur 6, 12, and 18 weeks following baseline. Participants will update their current medications and health care services. Additionally, sleep questionnaires, concussion symptoms, and mood questionnaires completed during baseline will be completed at reassessments.

### Randomization

Following the baseline assessment, participants will be randomized to either the CBT-I initial group (n=20) or the CBT-I WLC group (n=20; Figure 1). A randomization list was developed using SPSS [46]. Participants are not blinded to their group assignment. One researcher (RL) is providing the treatment for this study and is not blinded to group allocation. Questionnaires are sent to participants via REDCap, and participants will be able to answer the questionnaires on their own time and in their own environment. The same researcher (RL) is also performing data analyses for this study.

This session involves discussing the sleep log and determining if adjustments are needed to the sleep schedule, reviewing the prior week’s goals, assessing global treatment gains, and discussing relapse prevention.

#### WLC Activities

During the wait period portion, the WLC group will be encouraged to continue participation in their typical activities including employment, appointments, and personal schedule. After the 6-week wait period, the WLC group will receive the full CBT-I intervention.

### Statistical Analysis

#### Sample Size

For this study’s power analysis, the effect size is set at 0.8, which is based on a prior study that had large effect sizes on insomnia (0.8) [28]. The SD is set at 1 and the α is set at .05. Therefore, the required sample size is 32 participants, which is anticipated on the basis of clinical experience that 10%-25% of participants will drop out of the study so an additional 8 participants will be enrolled; thus, 40 participants will be enrolled for a total of 20 participants in each group. Intention-to-treat analyses will be used; hence, in the event of a participant dropping out after randomization, the data from their last assessment will be carried forward to the reassessment [48].

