#### Statistical Approach

##### Aim 1: To Assess the Therapeutic Effect of CBT-I in Individuals With a Subacute Concussion on Insomnia Symptoms and Sleep Quality

An independent samples *t* test will be used to determine if there is a significant difference in percent change in the ISI (primary outcome) and PSQI between the CBT-I and the WLC conditions. To assess maintenance for each group, paired *t* tests will be used to determine if there is a significant difference at the following time points: from the reassessment following CBT-I (reassessment 1 for the CBT-I group; reassessment 2 for the WLC group) to the immediate reassessment following the typical activities period (reassessment 2 for the CBT-I initial group; reassessment 3 for the WLC group), and from reassessment following CBT-I to delayed reassessment (reassessment 1 to reassessment 3 for CBT-I group). The percentage of participants who meet the minimal clinically important difference (MCID) will also be reported (7 points for the ISI [36] and 3 points for the PSQI [39]). In the event that the data do not meet the assumptions for parametric *t* tests, nonparametric tests (Mann-Whitney *U* test for independent samples, and Wilcoxon signed rank test for paired samples) will be used.

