### Anticipated Limitations

Potential limitations related to the treatment response are as follows. First, it is unknown how each participant will respond to the CBT-I treatment with their current symptom burden. Enrolling participants who are within at least 4 weeks of their concussion was to obtain individuals who have relatively stable symptoms at the time of enrollment. Second, medication use and dosage may affect the treatment response to the CBT-I intervention. Therefore, information on medication will be collected at baseline and at reassessments to be included in statistical analysis if indicated. Third, participants will potentially be receiving care from other health care providers, which could impact the interpretation of the results. Therefore, information on type of services being received will be collected at baseline and at reassessments to be included in statistical analysis if indicated.

Another potential limitation to this study is attrition. The attrition rate was 20% in one study evaluating CBT-I in adolescents with a concussion [28]. A 20% attrition rate was also observed in a cognitive behavioral intervention study on adults who have had a concussion [58]. To account for attrition, we will overenroll by 20% in this study. To help with retention, study procedures and time commitment will be clearly articulated to potential participants and reinforced during the course of the study. Furthermore, individuals in the WLC will be contacted by telephone in the middle of their 6-week waiting period to remind them of their upcoming CBT-I sessions and to maintain connection and interest.

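### The stated requirement of 32 participants does not follow from effect size 0.8, SD 1 and alpha .05: at 32 the planned t test has 59% power two-sided (71% one-sided)

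*Protocol article*

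**What the plan says.** The Sample Size section gives the planning inputs: "the effect size is set at 0.8, which is based on a prior study that had large effect sizes on insomnia (0.8"), and then "The SD is set at 1 and the α is set at .05". The next sentence draws the conclusion: "Therefore, the required sample size is 32 participants". It expects 10% to 25% of participants to drop out and adds 8, giving 40 in total and 20 per group. Analysis is by intention to treat, with the last assessment carried forward for dropouts. The section states neither a target power nor whether the test is one- or two-sided.

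The Aim 1 analysis fixes the test: "An independent samples *t* test will be used to determine if there is a significant difference in percent change in the ISI (primary outcome"), compared between the CBT-I and waitlist conditions.

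Anticipated Limitations cites two studies with 20% attrition and says "we will overenroll by 20% in this study". The Results section reports that enrolment of 40 was completed in July 2022.

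**The concern.** The figure of 32 is written as a consequence of the three inputs before it. For a two-group t test at a standardised difference of 0.8, 32 in total is well below the number needed at the usual power targets. A reader who takes the word required at face value will assume that the trial had a good chance of detecting the effect it was planned on.

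What is at stake is how the primary result is read. Without the true power figure, a non-significant difference on the Insomnia Severity Index (ISI) could be taken as evidence of no effect, when the design left a substantial chance of missing a true effect of 0.8 SD.

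**Working it through.** **Inputs**
- Standardised difference d = 0.8/1 = 0.8 and alpha = .05 (Sample Size).
- Independent-samples t test (Aim 1 analysis), 1:1 allocation.
- Totals of 32 (16 per arm) and 40 (20 per arm) (Sample Size).
- Sidedness is not stated. Two-sided is taken as the main reading because the test is for a significant difference; one-sided is shown beside it.
- Target power is not stated. 80% and 90% are taken as the conventional targets.

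**Trying to reproduce 32**

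Normal approximation, two-sided: n per arm = 2(z₁₋α/₂ + z_power)²/d².
- 80%: 2(1.960 + 0.842)²/0.64 = 24.5, so 25 per arm, 50 in total.
- 90%: 2(1.960 + 1.282)²/0.64 = 32.8, so 33 per arm, 66 in total.

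The noncentral t calculation raises these slightly:

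| Test | Total for 80% | Total for 90% |
|---|---|---|
| Independent t, two-sided | 52 (26 per arm) | 68 (34 per arm) |
| Independent t, one-sided | 42 | 56 |
| Paired or one-sample t, two-sided | 15 | 19 |

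None of these is 32. With d = 0.8, a total of about 32 corresponds to roughly 60% power two-sided (32 by normal approximation, 34 by t) or 70% to 75% one-sided (30 and 34 by normal approximation; 32 by t at 70%).

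**Power at the stated sizes**

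Noncentrality = d√(n/2), with 2n − 2 degrees of freedom.
- 16 per arm: 0.8√8 = 2.263, 30 df, two-sided critical value 2.042.
- 20 per arm: 0.8√10 = 2.530, 38 df, two-sided critical value 2.024.

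| Analysed | Two-sided power | One-sided power | d detectable with 80% power, two-sided |
|---|---|---|---|
| 32 | 59.1% | 71.4% | 1.02 |
| 40 | 69.3% | 79.9% | 0.91 |

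Normal-approximation check, two-sided: Φ(2.263 − 1.960) = 61.9% and Φ(2.530 − 1.960) = 71.6%.

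**Attrition step**
- 8/32 = 25% over-enrolment.
- 32/(1 − 0.20) = 40, so the step allows for 20% attrition.
- 32/(1 − 0.25) = 42.7, so 43 would be needed at the upper end of the stated dropout range; 40 × 0.75 = 30 would complete.

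**The case against.** **Sidedness.** The article does not state it, and the hypotheses are directional. One-sided, the enrolled 40 give 79.9% power. This stands, and it is why both sets of figures are shown. It does not rescue 32, which gives 71.4% one-sided.

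**Target power left to the full protocol.** An article may omit the target power, and that omission is not the point here. The point is that a number is presented as derived from inputs that do not produce it at 80% or 90% power.

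**An unstated baseline adjustment.** If 0.8 referred to raw scores, change scores with a baseline correlation of 0.7 would need 32 for 80% power. Analysis of covariance would need 34 at a correlation of 0.6 and 28 at 0.7. The article states no such correlation and plans an unadjusted t test on percent change.

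**Dropout.** A reader might infer that 25% dropout cuts the primary analysis to 30 people. The documents do not support this, because the last assessment is carried forward and all 40 are analysed. The relevant worry is that carried-forward values may dilute the group difference, so 69% is a best case.

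**Attrition wording.** The 20% in Anticipated Limitations follows two citations of 20% attrition and agrees with 32/0.80 = 40. What remains is loose wording, and no cover for the 25% end of the range.

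**Claimed adequacy.** A reader might infer that the trial is presented as adequately powered. The Background says only this: "Therefore, an adequately powered clinical trial is needed to evaluate if CBT-I enhances sleep outcomes in people with a concussion". It does not say that this trial is the one, and the abstract's conclusions call it a pilot.

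**Conclusion.** The sentence is wrong as written. With d = 0.8, SD 1, alpha .05 and the planned 1:1 independent-samples t test, 32 is not the required total at 80% or 90% power on either sidedness. Two-sided, it is 20 short of the 52 needed for 80%.

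The chance of missing a true effect of 0.8 is about 41% with 32 and 31% with 40 if the test is two-sided, or about 29% and 20% if one-sided. These figures assume that 0.8 is the standardised between-group difference on the analysed scale and that carrying values forward does not dilute it.

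The attrition discrepancy is a minor matter of wording. Nothing here shows how 32 was obtained, and the conclusion does not depend on knowing.

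**What to change.** Replace the sentence that states the requirement with:

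> With d = 0.8 and two-sided alpha .05, 16 per arm gives 59% power and 20 per arm 69% (one-sided: 71% and 80%); the effect detectable with 80% power, two-sided, is d = 1.02 (n = 32) or 0.91 (n = 40).

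State which sidedness applies. Add that 69% is a best case because carrying the last assessment forward may dilute the effect. Say that conclusions on the ISI will rest on the effect estimate and its confidence interval, so that a non-significant result is not read as evidence of no effect.

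Word the attrition text the same way in both sections: 8 added to 32 is 25% over-enrolment, which allows for 20% attrition and does not cover 25%.

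The change is to wording only and needs no further enrolment. Its downside is that the stated power becomes less favourable.

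### The required total of 32 is not reproduced at 80% or 90% power, one- or two-sided, for the planned independent samples t test

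*Protocol article*

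**What the plan says.** The Sample Size section gives three inputs. On the first it says "the effect size is set at 0.8", which it takes from a prior study's effect on insomnia. On the other two it says "The SD is set at 1 and the α is set at .05". It then concludes: "Therefore, the required sample size is 32 participants". Eight more are added against an anticipated dropout of 10% to 25%, giving 40, or 20 per group. So 32 is a total, 16 per group. No target power is given, and the test is not said to be one- or two-sided.

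The same section specifies intention to treat, with a dropout's last assessment carried forward.

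The Statistical Approach for Aim 1 fixes the primary test as an independent samples t test comparing CBT-I with waitlist, which "will be used to determine if there is a significant difference in percent change in the ISI (primary outcome) and PSQI". The Results section says that enrolment of 40 was completed in July 2022, with data collection expected to end in November 2022.

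**The concern.** With an SD of 1, the effect of 0.8 is a standardised difference. Once alpha and the test are fixed as well, the sample size depends only on power and sidedness. The claim can therefore be checked across every conventional choice of those two, even though the article states neither.

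A power analysis that ends in a required number tells the reader that the primary comparison reaches a customary power if that many participants are evaluable. If no customary power yields 32, the trial has a lower chance of detecting the effect it assumes than the sentence implies. This bears directly on the primary outcome.

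**Working it through.** **Inputs.** From Sample Size: d = 0.8/1 = 0.8, alpha = .05, 16 per group before dropout and 20 per group enrolled. From Aim 1: independent samples t test with two equal groups. Assumed, because not stated: power of 80% or 90%, and both one- and two-sided tests.

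**The dropout step.** 32 + 8 = 40, and 32/(1 − 0.20) = 40. This step is consistent with a 20% loss. The difficulty lies in the 32.

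**Trying to reproduce 32.** The normal approximation is n per group = 2(z_alpha + z_power)²/d².
- Two-sided, 80%: 2(1.960 + 0.842)²/0.64 = 24.5, so 25 per group.
- Two-sided, 90%: 2(1.960 + 1.282)²/0.64 = 32.8, so 33 per group.
- One-sided, 80%: 2(1.645 + 0.842)²/0.64 = 19.3, so 20 per group.
- One-sided, 90%: 2(1.645 + 1.282)²/0.64 = 26.8, so 27 per group.

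The noncentral t calculation, which is exact for this test, gives slightly larger numbers:

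| Test | Power | n per group | Total |
|---|---|---|---|
| Two-sided | 80% | 25.5, so 26 | 52 |
| Two-sided | 90% | 33.8, so 34 | 68 |
| One-sided | 80% | 20.03, so 21 | 42 (40 by the normal approximation) |
| One-sided | 90% | 27.5, so 28 | 56 |

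The smallest total in these four cases is 40 to 42. Run in reverse, about 16 per group appears only at roughly 60% power two-sided (16.3 per group) or 70% one-sided (15.4 per group).

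**Power that the numbers give.** The noncentrality is d·√(n/2).
- n = 16: 0.8·√8 = 2.263. Power is 59.1% two-sided and 71.4% one-sided.
- n = 20: 0.8·√10 = 2.530. Power is 69.3% two-sided and 79.9% one-sided.

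As a check on the two-sided figures, the normal approximation gives Φ(2.263 − 1.960) = 61.9% and Φ(2.530 − 1.960) = 71.6%.

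**Detectable difference.** At 80% power, two-sided, it is 0.91 SD with 20 per group and 1.02 SD with 16 per group.

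**Chance of missing a true 0.8 SD effect, two-sided.** 1 − 0.693 = 31% with 40 analysed, and 1 − 0.591 = 41% with 32.

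**The case against.** **Power and sidedness are unstated, so 80% and two-sided are the reviewer's choices.** This stands as a limit on how the point is worded. The article is condensed, and leaving out the target power is not in itself a fault. A reader might infer that 52 is the number the plan should have had. The document does not support that, because 52 depends on two assumptions it does not make. What it supports is narrower: a stated result, presented as following from stated inputs, is not reached at either customary power under either sidedness.

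**The hypotheses are directional, and a one-sided test gives the 40 enrolled about 80% power.** The arithmetic is right and belongs beside the two-sided figure. But Aim 1 tests for a significant difference without naming a direction, which reads more naturally as two-sided. Even one-sided, 32 gives 71%, and 32 is the number called required.

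**The 59% figure is not for the planned analysis.** This stands. Because dropouts' values are carried forward, the nominal analysis number is 40, so about 69% two-sided should lead. It may be optimistic. A treated participant who leaves before the first reassessment would enter with the baseline value and no change, which can dilute the effect.

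**Baseline adjustment could bring the number down.** An adjusted analysis with an assumed baseline-to-follow-up correlation of 0.6 would need 16.7 per group, so 17, or 34 in total, at 80% power. No such correlation is given and no adjustment for baseline ISI is planned. Covariates are named for the Aim 3 regressions, and elsewhere only medication and other services may be included if indicated.

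**Further inferences a reader might draw.**
- A paired test at d = 0.8 with 16 people has about 85% power, so 32 could be twice a within-person figure. Nothing in the text says so.
- The Background says "Therefore, an adequately powered clinical trial is needed to evaluate if CBT-I enhances sleep outcomes", while the Abstract's conclusions begin "Successful completion of this pilot study". The first describes what the field needs and the second labels this study, so this is a tension in framing and adds nothing to the arithmetic.
- A null result might be taken as evidence against CBT-I, but the document does not say how one would be interpreted.

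**Conclusion.** The point holds in this form: for effect 0.8, SD 1, alpha .05 and an independent samples t test, a total of 32 follows at neither 80% nor 90% power, one- or two-sided. With the 40 enrolled all analysed, power for 0.8 SD is about 69% two-sided or 80% one-sided, before any dilution from carried-forward values. If only 32 are evaluable it is 59% or 71%.

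That 32 is not reproduced does not depend on sidedness; the size of the shortfall does. The power figures assume equal groups and that 0.8 SD applies to percent change in the ISI, the variable tested. The article gives no SD for that variable, so the detectable differences cannot be turned into percentage change from the document alone.

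**What to change.** Do not enrol more; enrolment is complete. In Sample Size, delete the word *required*, state whether the test is one- or two-sided, and replace the sentence with the power achieved. If the test is two-sided:

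> With 40 participants analysed, a two-sided independent t test at .05 has about 69% power for a 0.8 SD difference (59% if only 32 are evaluable); the difference detectable with 80% power is 0.91 SD (40) or 1.02 SD (32).

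Report the primary result as the between-arm difference with its 95% CI, so that the precision is visible whatever the p value.

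The cost is wording only. The downside is that the stated figure becomes less favourable than the present sentence implies.
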